#### Randomisation and blinding

Participants will be randomly assigned equally to the two study groups with the use of simple randomisation, in which a third-party statistician will use computer software to generate pseudorandom numbers. Only the clinical data manager will have access to the random number table in the computer. Subjects will be enrolled by a research assistant in the order of enrolment time. Allocation will be made by the clinical data manager using the random number table. The statistician will be blinded to the allocation of subjects during the statistical analysis.

Since the surgical operator and the observer must know which group each subject has been assigned to, they cannot be blinded. The study has a single-blind design in which the investigators will be aware of the surgical procedures used in the different trial groups, but the participants will be unaware of them.

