### Relevant concomitant care permitted or prohibited during the trial

#### Perioperative management

After the operation, a fluid diet will be given for 1 day, and appropriate fluids will be supplemented. Nonsteroidal anti-inflammatory drugs or opioid central analgesics will be given for postoperative pain according to the VAS pain score. For postoperative urinary retention, catheterisation will be determined by the ward doctor on duty after evaluating the patient’s symptoms and signs. The patient’s catheter will be removed on POD 2. For postoperative defecation, lactulose oral solution will be used to soften the stool on the first day after the operation. If the patient still has difficulty defecating, a glycerine enema will be administered to help the patient defecate. If the symptoms still cannot be alleviated, warm normal saline can be given as a cleansing enema.

Twenty-four hours after the operation, the anal canal dressing will be removed, and the patient can defecate on their own. After defecation, the patients will be treated with heat-clearing and detoxifying traditional Chinese medicine sit-baths, iodophor disinfection, indomethacin and furazolidone embolisation of the anus, and dressing changes every day after defecation. The patient’s wound recovery, stool smoothness, and blood in the stool will be evaluated in the decision to arrange for discharge. After discharge, the patient will be advised not to exercise vigorously, continue perianal disinfection and dressing changes, and participate in regular outpatient follow-up.

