#### Strategies to improve adherence to interventions

Our strategy to improve follow-up monitoring compliance includes face-to-face adherence reminders by the surgeon at regular postoperative follow-up visits. In addition, we will ask patients during the visit how best to contact them (e.g. phone, WeChat, text message). The method of reminding patients to attend follow-up visits to the questionnaire will depend on their preferred method of contact.

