### Outcome measures

#### Primary outcome measures

The primary outcome measures are postoperative incision healing time and the time to return to normal activities, calculated in days (d) [20, 25]. The healing criteria are as follows: complete epithelialisation of the anal canal and perianal skin. The rectal mucosa should be intact, without ulcer or erosion.

Efficacy evaluation: Efficacy will be evaluated according to the efficacy evaluation for mixed haemorrhoids in the 2017 Standard for Diagnosis and Efficacy of TCM Diseases and Syndromes as follows: cured: the symptoms and haemorrhoids disappear; improved: the symptoms improve and the haemorrhoids shrink; and unhealed: there are no changes in symptoms and signs.

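### Return to normal activities is a primary endpoint with no stated criterion, recorded by an observer who knows the arm, while patients are under open-ended advice against vigorous exercise

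*Protocol article*

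**What the plan says.** Under Primary outcome measures, the protocol article names two primary outcomes, both counted in days: incision healing time and time to return to normal activities. The criteria that follow concern healing: "complete epithelialisation of the anal canal and perianal skin", plus intact rectal mucosa. The section does not say which activities count as normal, or who supplies the date. The Statistical analysis and Primary efficacy assessments sections repeat both endpoints and declare superiority on recovery time at one-sided 0.025.

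Perioperative management, written as common care for both arms, contains two statements that touch this endpoint. On leaving hospital: "wound recovery, stool smoothness, and blood in the stool will be evaluated in the decision to arrange for discharge". On the period afterwards: "After discharge, the patient will be advised not to exercise vigorously". No end to the advice is given.

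Randomisation and blinding states: "Since the surgical operator and the observer must know which group each subject has been assigned to, they cannot be blinded". It adds that "the investigators will be aware of the surgical procedures used in the different trial groups, but the participants will be unaware of them". Data collection and management has the evaluators of the results fill in the case report form.

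**The concern.** Healing is judged against a described physical finding. Return to normal activities has no such anchor, and the protocol's own care leaves a grey zone. A patient may have resumed work, housework and self-care while still avoiding vigorous exercise as told. One reader of the form would date recovery to the return to work, and another would wait until nothing is restricted. The article does not settle which is right.

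That ambiguity would be mostly noise if the recorder did not know the arm. Here the observer does. If grey-zone cases are resolved even slightly more generously for the new operation, the arms separate without any difference in recovery. Patient blinding limits this only if the date comes from the patient, and the article does not say that it does. At stake is a superiority claim on one of the two primary endpoints.

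**Working it through.** **Inputs.** From Sample size: means 10.50 (experimental) and 13.40 (control), SDs 3.46 and 3.66, two-sided 0.05, 33 per arm, 78 in total after 15% loss. From the analysis sections: one-sided 0.025, which has the same critical value in the favourable direction. Sample size does not name the endpoint behind its means, and power is not stated. Using its SD for return to activities is therefore an assumption.

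**Reproducing the plan's figure.**
- Common SD = √((3.46² + 3.66²)/2) = 3.56; planned difference = 13.40 − 10.50 = 2.90.
- At an assumed 90% power, the t-based solution is 32.7 per arm, rounded up to 33.
- 33/0.85 = 38.8, so 39 per arm and 78 in total.

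The stated size reproduces and is not in question here.

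**Effect of a recording gap between arms (gaps assumed; the documents give none).** Let b be the gap in days in favour of the new operation, with no true difference.
- Standard error = 3.56 × √(2/n) = 0.877 at n = 33 and 0.806 at n = 39.
- Noncentrality = b / standard error; for b = 1 this is 1.14 (n = 33) or 1.24 (n = 39).
- Probability of declaring superiority = P(noncentral t with 2n − 2 df exceeds the 0.975 t quantile), the quantile being 1.998 at n = 33 and 1.992 at n = 39.

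| Assumed gap b | 33 per arm | 39 per arm |
|---|---|---|
| 0 days (nominal) | 2.5% | 2.5% |
| 0.5 day | 8% | 9% |
| 1 day | 20% | 23% |
| 2 days | 61% | 69% |

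A 1-day gap is about a third of the planned difference (1/2.90 = 0.34).

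**Effect of a restriction common to both arms.** Suppose no patient in either arm can be recorded as recovered before day f (f assumed). Each time becomes max(T, f), with T normal at the planning values. The expected difference follows from E[max(T, f)] = f·Φ(z) + μ·(1 − Φ(z)) + σ·φ(z), with z = (f − μ)/σ. Power is by simulation at 33 per arm.

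| Earliest day f | Expected difference | Power |
|---|---|---|
| none | 2.90 | 90% |
| 7 | 2.7 | 90% |
| 10 | 2.1 | 88% |
| 14 | 0.9 | about 71% |

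The day-14 case is extreme: it would hold back about 84% of the experimental arm (Φ((14 − 10.5)/3.46)) and 57% of controls (Φ((14 − 13.4)/3.66)). Equal handling of the arms therefore costs little, and unequal recording is the mechanism that matters.

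**The case against.** A reader might infer more: that patients are told to limit activity in general, that unblinded staff keep them in hospital, and that the endpoint therefore measures staff decisions rather than recovery. The document does not support that.

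- The advice covers vigorous exercise only. It says nothing about work, housework or self-care.
- Discharge rests on wound recovery, stool and bleeding, which are themselves signs of recovery. A patient discharged sooner on those signs has, by the protocol's own markers, recovered sooner.
- The article does not say who decides discharge. A ward doctor on duty appears only in connection with catheterisation, and the blinding section does not mention discharging staff.
- The surgeon's "face-to-face adherence reminders by the surgeon at regular postoperative follow-up visits" are a means of improving follow-up compliance, not an occasion for relaxing activity advice.
- No difference in care between arms is described, and the patients who resume the activities are blinded. The article also admits that incomplete blinding may bias results.

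All of this stands. It removes any claim that bias has been shown, and any claim that the care itself is at fault.

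It can also be said that this is a journal article and that the full protocol or case report form may define the endpoint. That carries some weight. But the article does set out criteria for one primary outcome and not the other, and it pairs the undefined one with an unblinded observer and an open-ended restriction. A definition elsewhere would meet the point only if it also settled how the restricted exercise counts and whether the date comes from the patient. The admission about blinding comes with no safeguard for this endpoint.

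**Conclusion.** The point holds in a limited form. As described, a primary endpoint that depends on judgement has no criterion, its boundary is blurred by advice with no stated end, and the observer knows the arm. That is an avoidable risk of bias, worth correcting. It is not evidence that the arms are, or will be, handled differently.

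Its possible size is about 8% to 61% false superiority at 33 per arm (9% to 69% at 39) for recording gaps of 0.5 to 2 days, against a nominal 2.5%. Those gaps are assumptions, as is the use of an SD of 3.56 for this endpoint. The figures show how sensitive the test is and do not estimate what will happen. Dilution from care common to both arms is minor unless an extreme restriction is assumed.

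**What to change.** 1. Under Primary outcome measures, define the endpoint as the first day on which the patient resumes their own usual pre-operative daily activities. Reconcile this with Perioperative management by stating that the vigorous exercise restricted there is not part of the endpoint.
2. Take the date from the blinded patient, in answer to one fixed question worded identically in both arms. The observer transcribes the answer and does not judge it.
3. Record the day of discharge and report it by arm beside this endpoint, as a descriptive check only.

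Discharge criteria and activity advice stay with the investigators; no change to care is needed.

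The cost is a wording change to the protocol and case report form. Table 1 already places recovery time at follow-up visits within weeks 2 to 4, so no visit is added. The drawback is timing: Trial status reports recruitment about two thirds complete, so the endpoint will have been recorded in two ways. Patients recorded before the change should be identified, and a sensitivity analysis should show the result with and without them.

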#### Discharge and follow-up

Wound healing and surgical complications will be observed 1, 2, 3, and 4 weeks after the operation.

Each participant will be followed up 12 and 24 weeks after the operation via WeChat, telephone, video, and outpatient clinics. At 3 months and 6 months after the operation, the Cleveland Clinic Florida Fecal Incontinence Score (CCF-FI) will be used to evaluate the anal condition of the patients and to evaluate whether the patients have postoperative anal incontinence. The simple SF-36 quality-of-life questionnaire (homemade) will be used to evaluate the patients half a year after the operation.

For the schedule of the trial, please see Table 1.

#### Criteria for discontinuing or modifying allocated interventions

Criteria will not be applied because it is not possible for the study to change the allocation once the ultrasonic scalpel device is used during surgery. Patients will discontinue their participation in the study only if they experience a serious adverse event that may be related to the device.

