#### Participants

Eligible participants who meet the diagnostic criteria for haemorrhoids in the Clinical Diagnosis and Treatment Guidelines for Hemorrhoids (2006 edition), formulated by the Colorectal and Anal Surgery Group of the Chinese Medical Association Surgery Branch and the Anorectal Branch of the Chinese Society of Traditional Chinese Medicine, will be enrolled. All the participants will have been treated and hospitalised by the Department of Integrated Traditional Chinese and Western Medicine of West China Hospital of Sichuan University.

The trial has been approved by the Ethics Committee on Biomedical Research at West China Hospital of Sichuan University (Approval code: NO. 2020–367). It is also registered in the Chinese Clinical Trial Registry (Registration ID: ChiCTR2100047229).

Inclusion criteria.Patients with the clinical manifestation of mixed haemorrhoids with symptoms of internal haemorrhoids and external haemorrhoids existing at the same time. Among them, internal haemorrhoids should manifest as stage III (grade) or higher;Patients aged 20–70 years without obvious surgical contraindications;Patients who provide informed consent, with good compliance, and are able to cooperate to complete all clinical research content.

Exclusion criteria.Patients with haemorrhoids combined with anusitis;Patients with haemorrhoids combined with inflammatory bowel disease;Patients with suppurative infection around the anorectal canal;Patients with intestinal infectious diseases (e.g. dysentery);Patients diagnosed with outlet obstructive constipation.

Withdrawal criteria.Patients who exhibit poor compliance during the study, which can affect the effectiveness evaluation;Patients who have serious adverse events, complications and special physiological changes and are not able to continue the experiment;Patients who quit on their own volition during the study;Patients who withdraw from the trial, are lost to follow-up, or die due to various other reasons;Patients who have incomplete data that affect the validity judgement.

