#### Procedure for unblinding if needed

Participants with serious adverse events will be reported to the principal investigator and the Ethics Committee (IEC) of West China Hospital, Sichuan University, who will make the decision to unblind and withdraw them from the study.

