### Intervention description

#### The treatment group

The external haemorrhoids in the mother haemorrhoid area at points 3, 7, and 11 will be removed by an ultrasonic scalpel in a V-shape;The internal haemorrhoids will be clamped with forceps to be removed, the superior haemorrhoid artery will be ligated with No. 0 mousse thread “8”, 1 ml of Xiaozhilin will be injected under the ligation proximal sticking mould, and then the haemorrhoid will be removed slowly with an ultrasonic scalpel along the clamp mark at the base;The carbonisation (fixation) range of the incision will be checked, the free carbonised tissue will be removed at the incision, a needle will be inserted at the edge of the solidified tissue to suture the incision with the figure of “8” slightly above the tooth line, and then the incision epithelium will be sutured near the tooth line with the modified “8” suture method. When there is no obvious bleeding from the wound, the operation will be considered complete.

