#### Methods in analysis to handle protocol non-adherence and any statistical methods to handle missing data

Data will be analysed on the basis of the full analysis set (FAS), per-protocol set, and safety set. FAS analysis is a fundamental principle of intention-to-treat and will include all patients enrolled in this trial. Analyses will be performed according to the intention-to-treat principle, with patients assessed according to the group to which they were randomly assigned, regardless of actual use or algorithm adherence. The per-protocol analysis is a subset of the FAS analysis, which will include only patients who fully complete the trial. Safety set analysis refers to the set of patients who will be treated and evaluated for safety. Multiple imputation will be used to address missing values based on appropriate exploration of missing mechanisms and in accordance with good practice.

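### The rules on when a patient leaves the study contradict each other and, after a one-time operation, can stop outcome collection for reasons tied to outcome

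*Protocol article*

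**What the plan says.** Four places in the protocol article govern departure from the study.

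- *Criteria for discontinuing or modifying allocated interventions*: "Patients will discontinue their participation in the study only if they experience a serious adverse event that may be related to the device". The same paragraph identifies the device: "it is not possible for the study to change the allocation once the ultrasonic scalpel device is used during surgery".
- *Participants*, withdrawal criteria: five grounds with no restriction by arm. They are poor compliance that affects the evaluation; "Patients who have serious adverse events, complications and special physiological changes and are not able to continue the experiment"; the patient's own choice; withdrawal, loss to follow-up or death for other reasons; and "Patients who have incomplete data that affect the validity judgement". The recruitment section adds that these criteria are to be applied strictly.
- *Procedure for unblinding if needed*: SAEs in either arm go to the principal investigator and the ethics committee, "who will make the decision to unblind and withdraw them from the study".
- *Safety and reporting of serious adverse events*: the same reporting route, with withdrawal left open as a case-by-case decision.

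The section on non-adherence and missing data keeps all enrolled patients in the full analysis set by randomised group, whatever treatment was used or adhered to. It states "Multiple imputation will be used to address missing values", and it defines a per-protocol set "which will include only patients who fully complete the trial".

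**The concern.** The intervention is a single operation. Once it is done there is no treatment left to stop, so a rule that ends participation can in practice end only follow-up. The article does not say that follow-up continues after a patient leaves.

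The grounds for leaving include SAEs and complications. These are trial outcomes themselves, or are plausibly linked to slow healing. If follow-up ends there, the two primary outcomes (healing time and time to normal activities) and any later adverse events can be missing because the patient did badly. Under the device-related rule taken literally, this can happen in one arm only. Both features work against an unbiased comparison, and any resulting error would probably favour the new operation.

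**Working it through.** **1. Do the rules agree?** No.

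| Section | Who may leave | Arm |
|---|---|---|
| Discontinuing interventions | only after an SAE possibly related to the device | test only, read literally |
| Participants | any of five grounds | both |
| Unblinding | after an SAE, by decision | both |
| Safety reporting | after an SAE, by decision | both |

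The word *only* in the first row excludes most of what the other rows allow. The one-arm property follows from the two operation descriptions. In the test group the external haemorrhoids "will be removed by an ultrasonic scalpel in a V-shape"; the control description names forceps, incision and ligation but no ultrasonic scalpel.

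**2. Can a patient leave before the primary outcome is seen?** Yes. Healing is observed up to week 4 and adverse events to month 6. In the sponsor's 12-patient series of the open technique, bleeding came 5 to 16 days after operation. A patient who left after such an event could have no observed healing time.

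**3. Does the analysis section conflict with the withdrawal grounds?** Yes, in two places. Withdrawing a patient for incomplete data conflicts with imputing missing values. Withdrawing a patient for poor compliance conflicts with analysing patients as randomised whatever their adherence.

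**4. The plan's own figures.** The sample size is not in dispute. With means 10.50 and 13.40, SDs 3.46 and 3.66 (root mean square 3.561) and two-sided 0.05, a noncentral t calculation gives 33 per group at 90% power. Power is not stated; 90% is inferred because it returns 33. Then 33/0.85 = 38.8, so 39 per group and 78 in total.

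**5. Illustration of size.** Assumptions, none of them in the documents:
- k of the 39 test patients are lost, with true healing at h days;
- the other test patients average 10.5 (the sample-size section names neither outcome nor unit for this figure; it is read here as days to healing);
- the lost patients are left out, or are imputed at the average of those who stayed;
- no comparable loss occurs in the control arm.

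Understatement of the test mean = k × (h − 10.5) / 39.

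| k | h | True test mean | Understated by |
|---|---|---|---|
| 2 | 21 | 11.04 | 2 × 10.5/39 = 0.54 |
| 2 | 28 | 11.40 | 2 × 17.5/39 = 0.90 |
| 4 | 21 | 11.58 | 4 × 10.5/39 = 1.08 |
| 4 | 28 | 12.29 | 4 × 17.5/39 = 1.79 |

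**6. How far this depends on the assumptions.** If imputation recovered half of the excess healing time, half of each figure would remain (0.27 to 0.90 days). If the control arm lost the same number at the same h, and its other patients averaged 13.4, the net error in the difference would be k × (h − 10.5)/39 − k × (h − 13.4)/39 = k × 2.9/39. That is 0.15 days for k = 2 and 0.30 days for k = 4. Most of the illustrated error therefore comes from the one-sidedness of the loss and from uninformative imputation.

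**The case against.** A reader might infer that the worst outcomes leave the analysis, from one side. The documents do not support that.

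- **Leaving the analysis.** The full analysis set keeps every enrolled patient as randomised and imputes missing values. The consent provisions also ask participants whether their data may be used if they choose to withdraw. What is lost is later observation and per-protocol membership.
- **From one side.** Only the device-related rule is confined to the test arm. The other three sections cover both arms.
- **Automatic withdrawal.** The Participants criterion also requires that the patient cannot continue, and the unblinding and safety sections leave the matter to a decision. That decision is not simply in the hands of unblinded staff: the ethics committee takes part, the principal investigator does not collect data, and an independent committee considers trial withdrawal.
- **Biased complication and safety results.** The event that prompts withdrawal has already been recorded. A bleed needing surgery already scores the top bleeding grade. Only events after departure could be missed.
- **Imputation.** The model is not shown and may properly sit in the analysis plan. It could use bleeding scores recorded before departure.
- **The 4 of 12 reoperations.** These followed open, unsutured surgery, and the trial operation was modified because of them. They are no forecast for this trial.

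All of this stands and limits the point. It does not remove the contradiction between the sections. Nor does it restore outcomes that were never collected: imputation under missing at random may still understate long healing times, and how well a model could correct this cannot be known in advance.

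**Conclusion.** The point holds in limited form. The sections on withdrawal, discontinuation, unblinding and safety reporting contradict each other. If followed as written, they allow follow-up to end for outcome-related reasons, and under one rule in the test arm only. That follow-up ends when a patient leaves is an inference: the article does not say so outright, but nothing in it says otherwise, and no treatment remains to be stopped. The full analysis set reduces the harm but would rest on imputed primary outcomes for these patients; the per-protocol set leaves them out. The size and even the presence of bias are unknown. The 0.5 to 1.8 days is an illustration on assumed counts and healing times with no control losses, and should not be read as an estimate.

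**What to change.** - Reconcile the four sections so that they give one consistent statement of when a patient leaves the study. Which clinical rule applies is for the sponsor to settle.
- Separate stopping participation or treatment from stopping data collection. Follow every randomised patient who still consents on the existing schedule after any SAE, complication, non-compliance or missing item.
- No longer treat incomplete data or poor compliance as grounds to end data collection.
- Analyse these patients in the full analysis set with their observed times. With follow-up continued, fewer would fall out of the per-protocol set for this reason.
- Add a sensitivity analysis for data not missing at random, for example with longer healing times imputed after an SAE.

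The cost is protocol wording, its ethics submission, and continued contact with a few patients on visits already scheduled. The article reports recruitment about two-thirds complete, so the change should come soon: follow-up not collected at the time may be unrecoverable.
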